**1.1. PROTOCOL SYNOPSIS**

**A Pilot Trial of Glucosamine and Chondroitin Effects (GLANCE)**

Chronic inflammation is associated with carcinogenesis. Increased serum concentrations of C-reactive protein (CRP) have been associated with human cancer risk. Glucosamine and chondroitin (G&C) are among the most commonly used dietary supplements in the US. In vitro and limited animal studies show that G&C have anti-inflammatory properties, including inhibition of Nuclear Factor-kappa B (NF-kB), a transcription factor and central mediator in the immune response. In a large prospective study of the association of dietary supplement use and cancer risk, we found that use of G&C was associated with a 26-35% risk reduction of lung and colorectal cancer, and a 16-17% reduction in total mortality; the strongest and most consistent results across endpoints of a beneficial effect of any supplement studied so far. Our goal in the proposed study is to examine the effect of G&C on objective markers of inflammation in order to evaluate its potential as a chemopreventive agent. Metabolomics analyses will also be carried out in serum to determine other potential mechanisms of action of G&C.

**Design:** A randomized, placebo-controlled trial

**Sample Size:** Recruitment of 30 participants with the goal of having 20 finish

**Participants:** Men and women

**Selection:** Individuals from the Greater Seattle area who are overweight (BMI of

25-30 kg/m2) and between the ages of 20-55

**Exclusion:** Exclusion criteria address medical and practical issues: 1) chronic medical illness,

history of gastrointestinal, hepatic, or renal disorders, or inflammatory conditions

(including autoimmune and inflammatory diseases); 2) pregnancy or lactation; 3)

currently on a weight-loss diet; 4) BMI (body mass index) <25 or >30 kg/m2; 5) alcohol intake

of greater than 2 drinks/day (2 drinks being equivalent to 720 ml beer, 240 ml wine or

90 ml spirits); 6) current use of prescription or over-the-counter medications other than

multivitamin pills or infrequent use of aspirin and NSAIDs, including oral contraceptives

and hormone-secreting IUDs, or use of aspirin or NSAIDs more than 2 days per week;

7) abnormal renal, liver or metabolic test 8) inability to swallow pills; 9) known allergy to

shellfish; 10) not willing to take pills made from shellfish or animal sources; 11) intention

to relocate out of study area within next 4 months; In the event that we cannot recruit

sufficient participants within a BMI range of 25-30, we will expand eligibility to

5<BMI<32.5.

**Intervention:** a) Placebo and b) an over-the-counter glucosamine and chondroitin supplement

(1500 mg and 1200 mg, respectively)

**1.2. BACKGROUND/SIGNIFICANCE**

Use of dietary supplements and aspirin is routinely adopted by the US public to reduce risk of chronic diseases, including cancer. Chronic inflammation contributes to carcinogenesis, and biomarkers of inflammation [e.g., C-reactive protein (CRP)] have been associated with cancer risk. Use of aspirin, an anti-inflammatory drug, has have been shown to reduce colorectal and lung cancer risk in randomized controlled trials. However aspirin and other non-steroidal anti-inflammatory agents have not been recommended for cancer chemoprevention due to their associated adverse effects.

Glucosamine and chondroitin (G&C), often taken together in a single pill, are the most commonly used non-vitamin, non-mineral “specialty” supplements in the US. They are considered safe with no known major adverse effects. Laboratory studies show that G&C inhibit the transcription factor Nuclear Factor-kappa B (NF-kB), leading to reduced expression of inflammatory genes and inhibition of cell proliferation, effects associated with lower cancer risk. Several lines of evidence support a possible role for G&C in reduction of inflammation and cancer. In a large prospective cohort study over a 10-year period (n=77,738), we observed a 26-28% reduction in lung cancer incidence, a 27-35% reduction in colorectal cancer risk, and a 16-17% reduction in total mortality with use of G&C. These effect sizes are comparable to those reported for aspirin. In addition, in a nationally representative sample of 10,000 adults (NHANES), we found that regular use of G&C was associated with ~20% reduced levels of CRP, a well-recognized marker of inflammation (*Am J Epidemiol, in press*). Furthermore, increased CRP has been associated with cancer risk in several observational cohort studies.

Despite these intriguing results, and evidence for biologic mechanisms, to date there have been no human intervention trials evaluating the potential for G&C to reduce inflammation or alter other pathways relevant to carcinogenesis in humans. Our previous findings, representing the only evidence on G&C in humans, are observational and are thus subject to bias. A randomized controlled trial (RCT) would directly assess the effect of G&C on inflammation while maximizing internal validity. We propose to conduct a pilot RCT using a crossover design of 2 treatments—placebo and G&C — in a sample of 30 overweight participants, 20-45y. We will test the effect of G&C on the circulating inflammatory biomarker CRP and serum metabolomic patterns. Metabolomics measures a broad range of metabolites present in a biologic sample to permit the characterization of whole-system responses to an exposure, and will allow us to explore other potential pathways modulated by G&C.

**1.3. SPECIFIC AIMS:**

1. To determine the effect of a common starting dose of G&C [1500 mg/d glucosamine hydrochloride + 1200 mg/d chondroitin sulfate] on serum hsCRP concentrations.

2. To characterize the intervention-induced changes in serum metabolomic patterns via pathway analyses in response to G&C as compared to placebo.

We hypothesize that treatment with G&C will reduce serum hsCRP concentrations. We further hypothesize that the serum metabolomic patterns will differ between treatment groups, however, this aim is exploratory as there is very little known about the mechanisms of action of G&C. This analysis will be instructive in determining unknown pathways that might be affected by G&C.

**1.4. STUDY DESIGN**

The study is designed as a randomized, cross-over, placebo-controlled intervention of G&C and placebo. We will randomize participants to one of the two treatment orders, either G&C first followed by the placebo in the second period or the placebo first followed by G&C. Each treatment will be 28 days in duration with at least a 28 day washout period between treatments. Blood will be drawn once at baseline and at the end (Day 28) of each treatment period. In the case of illness, and during Days 1-3 of a women’s menstrual cycle, participants will delay the start or end of a treatment sequence and corresponding clinic visit in order to avoid blood draws during transitory spikes in the inflammatory biomarkers of interest.

**1.4.a. G&C Supplements**

The active treatment period will include 1500 mg/d glucosamine hydrochloride + 1200 mg/d chondroitin sulfate. The test agent and placebo will be provided by NutraMax, a well-established supplement company that follows Good Manufacturing Practices.

**1.4.b. Safety and Adverse Effects**

G&C are among the most commonly used non-vitamin, non-mineral over the counter supplement in the U.S. Though there are many short-term studies in humans evaluating its efficacy in treating osteoarthritis, few adverse events have been reported. The largest human trial, GAIT, conducted in men and women ≥40y, had 952 participants total in the three G &/or C arms, and a duration of 24 weeks. In that trial, 3.7% of participants withdrew due to adverse effects. Only two adverse events were attributed to G&C treatment: chest pain in a subject receiving G and congestive heart failure in a patient receiving combined treatment; but no rationale for the attributions to the treatment were given. Other side effects were mild, e.g., stomach upset, and were evenly spread across treatment groups, including placebo. Because G contains a sugar moiety, one concern had been that it may induce or worsen insulin resistance. However, a recent review of the human and animal studies concluded that G does not cause glucose intolerance nor does it affect glucose metabolism. In many countries, G&C are approved drugs based on their safety and efficacy. The European League Against Rheumatism (EULAR) rated G as having a safety profile of 5 on a 0-100 scale and C a 6, two of the safest drugs for osteoarthritis. There are no known adverse drug-drug interactions with G or C. Based on follow-up of the VITAL cohort study of 77,000 men and  women,  those who used glucosamine (with or without chondroitin ) at baseline were at  16% lower risk of death (HR= 0.82; 95% CI (0.75-0.90)), 12% lower risk of CVD death (HR=0.88 (0.74-1.06)) and 13%  lower  risk of death from  cancer  (HR = 0.87 (0.76-0.98)).

**1.4.c. Summary of Study Activities and Measures**

| **Baseline** | | **Reason for Measures** |
| --- | --- | --- |
|  | Screening Questionnaire Exclusion criteria  Information session & Informed Consent | |
|  | Health and Demographics Questionnaire | Data collection |
|  | Food Frequency Questionnaire (FFQ - FHCRC) | Ascertain dietary intake |
|  | Blood draw | Liver and kidney function panel |
|  | 12 h urine collections | Future measures (e.g., PGE)  Treatment compliance (G&C metabolites)  Completeness of urine collection (creatinine) |
|  | DXA scan | Ascertain body fat % |
| **Randomized, cross-over with 2 intervention periods: G&C and placebo** | | |
|  | Fasting blood draws (end of each period) | hsCRP concentrations;  Metabolomics analysis  Future measures (e.g., proteomics) |
|  | 12 h urine collections (end of each period) | Future measures (e.g., PGE-M, F2iso)  Treatment compliance (G&C metabolites)  Completeness of urine collection (creatinine) |
|  | Spot urine (women; beginning of each period) | Rule out pregnancy |
|  | Daily calendar, pill check-off | Compliance |

**1.5. STUDY POPULATION/RECRUITMENT**

Participants will be healthy, non-smoking men and women, ages 20-55 y, who are overweight [body mass index (BMI) ≥25 and ≤30 kg/m2]. We will recruit study volunteers by distributing flyers throughout the community and local institutions of higher education and creating a study website. All recruitment materials will provide a description of the study and contact information. Study information and an initial screening questionnaire will be available online, which can be submitted through electronic or ground mail. A contact telephone number and email address will also be provided for individuals who want to be mailed an information packet. The screening questionnaire will include questions on medical history, medication use, etc, that relate to eligibility. The prospective participant will be given information about the study including: attendance requirements, time commitments, as well as information about the intervention study. Interested persons will return the completed questionnaire to the study staff, who will determine eligibility and will contact eligible persons by phone or email to schedule a meeting. A packet containing a confirmation letter and the screening study consent form will be sent to the person prior to attending the meeting. Participants eligible to enter the intervention will meet with our staff to discuss all the details and expectations of the study, review informed consent and answer any questions they might have.

**1.6. ELIGIBILITY CRITERIA**

Inclusion: Healthy men and women aged 20-55 years who are overweight (BMI of 25-30 kg/m2)

Exclusion: 1) chronic medical illness, history of gastrointestinal, hepatic, or renal disorders, or

inflammatory conditions (including autoimmune and inflammatory diseases)

2) pregnancy or lactation

3) currently on a weight-loss diet

4) BMI (body mass index) <25 or >30

5) alcohol intake of greater than 2 drinks/day (2 drinks being equivalent to 720 ml beer,

240 ml wine or 90 ml spirits)

6) current use of prescription or over-the-counter medications, including oral

contraceptives and hormone-secreting IUDs, or use of aspirin or NSAIDs more than 2

days per week

7) abnormal renal, liver or metabolic test

8) inability to swallow pills

9) known allergy to shellfish

10) not willing to take pills made from shellfish or animal sources;

11) intention to relocate out of study area within next 4 months

**1.7. SPECIMEN AND DATA COLLECTION**

**17.a. Blood** We will obtain 12-hour fasting blood samples at baseline for clinical chemistries (to confirm eligibility) and at the end of each 28-day intervention period. Participants will come to the Prevention Center where certified personnel will collect four 10-ml vacutainers of blood; two containers will be used for the present study and two will be stored for future use, e.g., proteomics, with obtainment of additional funding. Specimens will be stored at -80ºC.

**17.b. Urine** Participants will collect a 12-hour urine at baseline and at the end of each intervention period. Volume will be measured and urine stored at -80ºC. These samples will be used for future measurement of prostaglandin E (PGE-M), a surrogate for COX-2 enzyme activity involved in the inflammatory cascade, and other future assays.

**17.c. Dietary Assessment** We will use an established, validated food frequency questionnaire (FFQ) to characterize food and nutrient intakes of the study participants over the 3 months prior to baseline.

**17.d. Body Fat (BF)%** Although we will recruit overweight individuals with a BMI between 25-30, there will still be a range of BF%. Thus we will use Dual-X-ray absorptometry (DXA) in the Prevention Center to accurately ascertain BF%.

**1.8. LABORATORY PROCEDURES**

**1.8.a. Urinary Creatinine** concentrations, measured on a COBAS Mira analyzer, will be used to adjust for variation in 12-h urinary collections. Urines will be used for PGE measurement when future funds are obtained.

**1.8.b. Serum hsCRP Assays** We will measure hsCRP using CRP Ultra Wide Range reagent(Genzyme, Framingham, MA) on a Roche Cobas Mira Plus Chemistry Analyzer. Samples will be run in duplicate with blinded QCs in each batch; any sample with duplicate coefficients of variation >10% will be re-analyzed. Any extreme values will be excluded, determined by values >5 standard deviations (SD) from the median and >2 SD from any other data point, in order to eliminate any potential acute inflammatory states at any time points.

**1.8.c.** **Serum Metabolomics Analysis** Assays will be performed by Metabolon ([www.Metabolon.com](http://www.Metabolon.com/)) using patented, proprietary methods for detection and quantification. The analysis utilized 3 analytical platforms, LC/MS/MS(+ESI), LC/MS/MS(-ESI) and GC/MS, to separate and detect a broad range of small molecules (LC-MS/MS spectra). Once ions of interest are identified, their chemical identities are matched against an in-house standardized library of >3,000 human metabolites.

**1.9. DATA ANALYSIS**

**1.9.a. Data Handling and Quality Assurance Procedures** All participants enrolled in the study will be issued a computer-generated study ID. This ID will be used on all participant questionnaires and forms, specimen tracking forms, and cryovials. This method maintains participant confidentiality and facilitates data management. The labels used on the cryovials for the blood and urine samples are freezer-proof. Study data are identified by ID number only. A password-protected file links the participant name with the study ID.

**1.9.b. Data Analysis** All statistical analyses will be conducted using STATA (v12) software. We will examine the distributions of the baseline characteristics and the primary outcomes of the study participants. We will characterize the distributions using scatter plots, histograms, and summary statistics (e.g., mean, median, standard deviation, quartiles, range) to identify extreme outliers and assess normality. If the test indicates that the distribution is not normal or is skewed, then we will perform appropriate transformations prior to our primary analyses. From our experience and relevant literature, the logarithmic transformation is appropriate for the inflammatory biomarkers.

**1.9.c. Testing of Specific and Secondary Aims**

**Specific Aim 1:**

We will use a generalized estimating equation (GEE) modification of linear regression. This method will allow us to account for within-person variation over time as well as the correlation between the intervention-induced changes within an individual. The dependent variable lnCRP will be denoted by Yit of ith participant at time t, where t is 0 or 1 for either the beginning or end of each treatment period. Let Xi be the indicator variable for the intervention period with G&C. The linear model takes the form:

E[Yit] = 0 + 1 t + 2 Xi + 3 Xi t ; Var[Yij] = 2, Cov[Yij, Ykl] = 2 if i = k and j  l, and 0 otherwise.

The parameter 3 is our main interest for Specific Aim 1 which represents the mean difference in CRP change from the pre- to post-treatment between the G&C and the placebo periods. Adjustment for potential confounders may not be needed due to randomization; however, we will evaluate other covariates for the purpose of reducing any unexpected confounding effects. All statistical tests will be two-sided with α set at 5%.

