**Specific Aim 2:**

Statistical differences in serum metabolites between experimental groups will be evaluated using paired t-tests and False Discovery Rates (q-values).

**Power and Sample Size Considerations.** Our study is designed to yield 20 participants who will

complete the study. Based on the mean and SD for CRP in the 1999-2000 NHANES data restricted to our inclusion criteria (20-55y and BMI 25-30) and an intra-class correlation coefficient for CRP ranging from 0.60-0.80, we estimate 80% power to detect a 40-56% change in CRP with the probability of a type I error set at 0.05. As with any pilot study our power is limited. However information from this pilot study will be used to support a future R01 submission for a larger RCT, including information on: methods of recruitment and compliance, estimated effect size from a randomized trial and sample size needed, and new G&C pathways that may serve as additional biomarker endpoints.

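### Aim 1 commits to GEE with about 20 participants; under ordinary z inference the test runs at about 6–7%, not the stated 5%

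*Protocol*

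**What the plan says.** Section 1.9.c of the protocol (Specific Aim 1) fixes the method for lnCRP: "We will use a generalized estimating equation (GEE) modification of linear regression". The model has terms for time, treatment period and their interaction, with a constant variance and one common within-person covariance. The interaction is the target; it "represents the mean difference in CRP change from the pre- to post-treatment between the G&C and the placebo periods". There is no term for period order. On the level, the section says "All statistical tests will be two-sided with α set at 5"%.

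The sample-size paragraph says "Our study is designed to yield 20 participants" who complete. The synopsis has "Recruitment of 30 participants with the goal of having 20 finish", so up to (30 − 20)/30 = 33% may be lost. Section 1.4 says of the allocation: "We will randomize participants to one of the two treatment orders".

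Section 1.9.b names Stata 12 but no command or options. Nothing in the protocol says whether standard errors are model-based or robust, or whether the reference distribution is z or t. For the exploratory metabolomics aim, by contrast, the protocol chooses paired t-tests.

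**The concern.** GEE tests are justified as the number of independent clusters grows. Here the cluster is the participant, and there are about 20. Two things go wrong at that size. The uncorrected sandwich variance is biased low, because it uses fitted residuals with no allowance for the estimated coefficients. A z reference then treats that variance as if it were known. Both push the false-positive rate above the nominal level and make intervals too short.

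This is more than a detail left for later, because the protocol has already chosen the method. With complete pairs and normal lnCRP, the design admits a test that is exact at any sample size: the t-test on within-person differences. The main aim is given large-sample inference while the exploratory aim is given t-tests.

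At stake are the standard error, p-value and interval for the hsCRP effect, which the protocol intends to use in planning a larger trial.

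**Working it through.** **Inputs.** Two-sided α = 0.05 (section 1.9.c); n = 20 completers and intra-class correlation 0.60–0.80 (sample-size paragraph). Assumed: normal lnCRP, complete pairs, a truly common within-person correlation, and equal numbers in the two orders (the ratio is not stated).

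**The plan's own figures.** The figure under test is the 5% level. The power statement (80% power for a 40–56% change) cannot be reproduced, because the SD taken from NHANES is not given. The level does not depend on that SD.

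**Uncorrected sandwich with z.** With complete balanced data, the GEE estimate of the interaction is the mean of Dᵢ, each participant's change on G&C minus change on placebo. The sandwich variance is Σ(Dᵢ − D̄)²/n², which is (n−1)/n times the usual s²/n. The z test therefore rejects when |t| > 1.96·√((n−1)/n):

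- 1.96 × √(19/20) = 1.91, and P(|t₁₉| > 1.91) = 7.1%. Simulation at n = 20 gives 7.1–7.2%; a standard GEE routine gives 6.8%.
- With a period term (not in the written model): 1.96 × √(18/20) = 1.86, and P(|t₁₈| > 1.86) = 7.9%.

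**Sandwich scaled by n/(n−1), still with z.** P(|t₁₉| > 1.96) = 6.5%; simulation gives 6.4–6.5%.

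**Model-based exchangeable errors with z.** With four observations per person the error degrees of freedom are 3 × 19 = 57.

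- P(|t₅₇| > 1.96) = 5.5%; with the √(19/20) factor, 6.1%. Simulation with dispersion denominator N gives 6.0–6.1%.
- With denominator N−p, simulation gives 3.4–4.6%; a standard GEE routine gives 4.7–5.2%.
- With two observations per person: 7.1–7.2% (denominator N) or 4.1–5.5% (N−p). One software run of this kind with a period term gave 12.5%, probably because of mixed denominators; I place no weight on it.

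**Corrected variance with t on 19 df** (critical value 2.093). Simulated level about 5%.

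**Sensitivity to the number analysed** (uncorrected sandwich with z):

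| n | written model | with period term |
|---|---|---|
| 15 | 7.9% | 9.1% |
| 18 | 7.4% | 8.3% |
| 20 | 7.1% | 7.9% |
| 30 | 6.4% | 6.9% |

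Errors drawn from a t₅ distribution barely change the n = 20 result (7.0%).

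**Interval width** (uncorrected robust z).

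- Written model: 1.91/2.093 = 0.913, about 9% too narrow; the correct interval is 2.093/1.91 = 1.096 times as wide.
- With a period term: 1.86/2.10 = 0.885, about 11.5% too narrow; the correct interval is about 13% wider.

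**Detectable effect at 80% power**, in SDs of the within-person difference. Normal formula: (1.96 + 0.84)/√20 = 0.626. Exact non-central t on 19 df: 0.660. The ratio is 1.05.

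**The case against.** The best reply is that the protocol names neither a z test nor a sandwich variance. A reader might infer that the trial's actual level is 7–8%, but that is a statement about one implementation. The constant variance and common covariance written in section 1.9.c fit model-based errors at least as well, and some versions of those hold 5% or less. The 7.9% also needs a period term that the written model lacks. This part of the objection stands, and the size must be stated conditionally.

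It can also be said that the variance estimator and reference distribution are normally settled in the statistical analysis plan, which is not shown, and that GEE with a suitable correction does reach 5%. That is true. It means the protocol's text does not contradict itself, and the remedy may already exist. But the protocol did fix a large-sample method for about 20 participants, and most standard ways of carrying it out exceed the level it states.

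Two further inferences are not supported:

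- **That GEE has nothing to offer here.** The synopsis allows for a third of participants to be lost, and section 1.8.b excludes extreme hsCRP values, so incomplete pairs are likely. GEE can use them, while a plain paired analysis drops them.
- **That the future application would inherit an inflated effect estimate.** Correcting the variance or the reference distribution leaves the point estimate unchanged. Only its apparent precision is overstated.

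**Conclusion.** The point holds in conditional form. With 20 completers and standard GEE z inference, the Aim 1 test runs at about 6–7% against a stated 5%: 7.1% for an uncorrected sandwich, 6.5% with the n/(n−1) factor, and about 6% for model-based exchangeable errors on four observations with denominator N. An N−p denominator can remove the excess. Adding a period term raises the uncorrected sandwich figure to 7.9%.

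These results rest on normal lnCRP, complete pairs, balanced orders and a common within-person correlation. Section 1.4 says "Blood will be drawn once at baseline and at the end (Day 28) of each treatment period", which can be read as three draws. In that case the second period has no pre-treatment value and the two-observation figures apply. That is a separate matter and does not alter this conclusion.

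Severity is minor. The trial is a pilot that acknowledges limited power, and the excess is about two percentage points for the written model.

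**What to change.** Keep the Aim 1 contrast and state small-sample inference for it. Either of these would do:

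- A within-person crossover t analysis: form each participant's G&C change minus placebo change in lnCRP and refer it to t on n−1 df, or n−2 df if period is adjusted for through treatment order.
- A linear mixed model with Kenward-Roger degrees of freedom, which also keeps participants with incomplete pairs. The team should confirm that the named Stata version supports this.

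If GEE is kept, specify a small-sample-corrected sandwich variance and a t reference with stated degrees of freedom.

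The change is a sentence or two in the protocol or the statistical analysis plan, made before data are seen. Compared with uncorrected robust z, intervals become about 10% wider (13% with a period term). The detectable effect grows by about 5% on the ln scale (0.660 against 0.626 SD of the within-person difference). The plain t analysis also loses incomplete pairs, which favours the mixed model if dropout is near the planned third.

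### The Aim 1 model needs hsCRP at the start and end of both periods, but hsCRP is scheduled only at the end of each, so the primary coefficient cannot be estimated as defined

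*Protocol*

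**What the plan says.** **Model.** Protocol section 1.9.c, Specific Aim 1, sets a linear GEE model for lnCRP with an intercept, t, X and the product of X and t. The time index is defined as "where t is 0 or 1 for either the beginning or end of each treatment period". X is defined by "Let Xi be the indicator variable for the intervention period with G&C". The product coefficient is the parameter of main interest and "represents the mean difference in CRP change from the pre- to post-treatment between the G&C and the placebo periods".

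**Sampling.** Section 1.7 (Blood) plans "12-hour fasting blood samples at baseline for clinical chemistries (to confirm eligibility) and at the end of each 28-day intervention period". The activities table in section 1.4.c agrees: the reason given for the baseline blood is "Liver and kidney function panel", and hsCRP appears only against the fasting draws at the end of each period. The only specimen that the table lists for the beginning of each period is a spot urine in women, to rule out pregnancy. Section 1.4 says "Blood will be drawn once at baseline and at the end (Day 28) of each treatment period" and separates the periods by a washout of at least 28 days.

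**Power.** The power paragraph in section 1.9.c claims 80% power with 20 completers to detect a 40-56% change in CRP, at ICC 0.60-0.80 and a type I error of 0.05. It prints no SD.

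**The concern.** A difference between two pre-to-post changes needs a pre and a post value in each period. The schedule gives no hsCRP before either treatment and no blood of any kind before period 2. The end-of-period-1 draw cannot stand in for the missing value: it is taken at the end of the other treatment, and the washout comes after it.

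The model and the sampling plan therefore describe different studies. Whoever runs the analysis will have to choose another parameter, or a way to fill in the missing time points, after the data are in. This is the analysis for the first aim of a pilot whose effect estimate is meant to support the sample size of a larger trial, so that choice should be made in advance.

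**Working it through.** Below, b0, b1, b2 and b3 are the coefficients of the intercept, t, X and X-by-t.

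**1. The plan's own figure.** Inputs from the power paragraph: n = 20, ICC 0.60-0.80, 80% power, 5% type I error (two-sided under Aim 1). The SD is not given, so I assume SD = 1 (on the log scale, or a raw SD equal to the mean). For a paired end-of-period contrast, the detectable difference is (1.960 + 0.842) × SD × √(2(1 − ICC)/20):
- ICC 0.80: 2.802 × √0.020 = 0.396
- ICC 0.60: 2.802 × √0.040 = 0.560

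This matches 40-56%. With SD 0.8 the range is 0.32-0.45, and with SD 1.2 it is 0.48-0.67. For a difference between two changes, the 2 under the root becomes 4. SD = 1 then gives 0.560-0.792, but an SD of about 0.71 brings it back to 0.40-0.56 (0.560 × 0.71 = 0.40; 0.792 × 0.71 = 0.56). The printed figure therefore fits either contrast, depending on an SD that the protocol does not state.

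**2. Needed against scheduled.**

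| Time point | Needed by the model | Blood scheduled | hsCRP listed |
|---|---|---|---|
| Start of period 1 | yes | one baseline draw | no |
| End of period 1 | yes | yes | yes |
| Start of period 2 | yes | no | no |
| End of period 2 | yes | yes | yes |

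**3. Estimability with hsCRP as scheduled.** Every observation has t = 1, so each row of the design matrix is (1, 1, X, X). The first two columns are identical, and so are the last two. For 20 completers there are 40 rows and the rank is 2 of 4. Only b0 + b1 and b2 + b3 can be estimated. The sum b2 + b3 is the end-of-period G&C-minus-placebo difference; b3 alone is not estimable.

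**4. If the one baseline sample were also assayed.** Assume 10 participants per sequence and exchangeable correlation, with σ² the variance of lnCRP.
- *Baseline entered as t = 0 in both periods.* For each person, (G&C end − baseline) − (placebo end − baseline) = G&C end − placebo end. The baseline cancels and b3 is exactly the paired end-of-period difference. Its variance is 2(1 − ICC)/20, which is 0.040σ² at ICC 0.60 and 0.020σ² at ICC 0.80.
- *Baseline attached to period 1 only, X main effect left free.* There are 60 rows and the rank is 4, so b3 can be fitted. However, b2 now comes from comparing the baselines of the two sequence groups. The variance of b3 is 2(1 − ICC)/20 + (2/10)(1 − 2·ICC²/(1 + ICC)).
  - ICC 0.60: 0.040 + 0.2 × 0.550 = 0.150σ², and 0.150/0.040 = 3.75
  - ICC 0.80: 0.020 + 0.2 × 0.289 = 0.078σ², and 0.078/0.020 = 3.9
- *Baseline attached to period 1 only, X main effect dropped* (randomisation implies that it is zero before treatment). The variance returns to 0.040σ² and 0.020σ².

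The same three draws thus give quite different precision according to a coding that the protocol does not specify.

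**The case against.** **Section 1.4 may intend a baseline draw in each period.** Read alone, its sentence on blood draws is ambiguous. The section also lets participants delay the start of a treatment sequence, with its clinic visit, to avoid draws during spikes in the inflammatory markers, which suggests that biomarker blood at the start was contemplated. Sections 1.4.c and 1.7 do not bear this out: they give one baseline draw, for eligibility. If per-period draws were intended, those two sections are wrong and the protocol still has to be reconciled.

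**Baseline blood could be assayed.** Section 1.7 collects four tubes, two of them for storage, without excluding the baseline visit, so this is possible. The model could then be fitted, and a reader who infers that it could never be run goes too far. What stands is that no period-2 starting value would exist, so the coefficient could not be estimated as the protocol defines it.

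**Substitutes need not be costly.** This is correct. A reader might infer that any workaround throws away most of the crossover's efficiency. Reusing the single baseline in both periods loses nothing; the large inflation belongs to one coding only.

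**Power.** A reader might also infer that the stated 80% really drops to about 51% (a change contrast with four draws) or 30% (baseline tied to period 1). Those figures presume that the 80% was computed for the end-of-period contrast. With no SD printed, the document does not establish that.

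**Notation.** X carries only a participant subscript, which might suggest a parallel-group model. The wording ties X to the period, so this is a matter of clarity.

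**The analysis plan may settle it.** The contradiction lies between the protocol's own model and its own schedule, so it is not a detail left for later.

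**Conclusion.** The primary analysis is wrong as written. On the hsCRP data that the protocol schedules, the coefficient named as primary is not estimable (rank 2 of 4). This depends on no assumption about SD, correlation or the split between sequences. With baseline blood also assayed, the coefficient still could not be estimated as defined, and its variance would range from that of the paired contrast (0.040σ² at ICC 0.60, 0.020σ² at ICC 0.80) to 3.75-3.9 times that. This range assumes 20 completers, 10 per sequence, exchangeable correlation and the protocol's ICC range.

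The design itself is sound on this point, because the end-of-period treatment difference can be estimated within person from the planned samples. Neither a general loss of efficiency nor a specific fall from the claimed 80% power is shown. The defect should be corrected before analysis, because it leaves the primary parameter to be chosen afterwards.

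**What to change.** In section 1.9.c, replace the model for Specific Aim 1 with one for the two end-of-period values: lnCRP of participant i in period p = mean + participant effect (or exchangeable within-person correlation under GEE) + period effect + τ·X_ip, where X_ip is 1 if participant i receives G&C in period p and 0 otherwise. Name τ, the end-of-period G&C-minus-placebo difference in lnCRP, as the primary parameter. Delete t and the X-by-t term, along with the description of the primary parameter as a difference in pre-to-post change. With equal sequences the period effect leaves the variance of τ at 2(1 − ICC)σ²/20.

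Restate the power paragraph for τ, giving the SD and the scale (log or raw) on which the 40-56% is expressed. Reword the draw sentence in section 1.4 so that it agrees with sections 1.4.c and 1.7.

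The cost is protocol wording, with no extra draw, visit or assay. The alternative is to keep the change contrast, which would need a blood draw before period 2 and hsCRP at the start of both periods. Under exchangeable correlation that contrast, unadjusted, has variance 4(1 − ICC)σ²/20, twice that of τ, so it is the more expensive choice and brings no gain in precision.
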